#### fMRI Measurements

For the fMRI measurements, detailed manuals are provided to the researchers who conduct measurements. Furthermore, researchers are trained before they conduct parts of the study with participants. During fMRI measurements, two researchers are present. Protocols will be written for fMRI measurements.

FMRI measurements are conducted in this session before (pre-fMRI) and after (post-fMRI) a short speech-gesture training of 30 min.

#### Stimuli

In order to gain an advanced understanding in the engine of integration mechanisms and their neural correlates in patients with schizophrenia, participants undergo fMRI measurements watching videos on a screen. The videos were recorded with an actor expressing concrete or abstract sentences (for an explanation of concreteness see “gestures in schizophrenia” in the background section). The videos were standardized, extensively evaluated and had been successfully applied in a large number of fMRI (13–15, 81), EEG (82), tDCS (65, 83) and patient studies including patients with schizophrenia (28, 29). Altogether, we use two categories of videos in the familiarization session: videos containing.

concrete sentences without gesture (S_CON)abstract sentences without gesture (S_ABS)

Videos from pre-fMRI measurement are repeated in post-fMRI measurement.

The videos’ sentences in the short speech-gesture training are repetitions from pre-fMRI measurement, but the videos this time are presented in two different modalities:without gesture (auditive modality: S),accompanied by gesture (bimodal: SG),

The videos were standardized, extensively evaluated and had been successfully applied in a study (84).

In the memory task after the post-fMRI measurement, sentences are presented to the participants in audio. The sentences are repetitions from the fMRI measurements and the short speech-gesture training.

We developed four different counterbalanced versions of stimuli presentation to avoid sequence effects.

#### fMRI Tasks

In the task during the pre- and post-fMRI measurement, participants are asked to decide whether the sentences presented to them were concrete or abstract (decision task). This allows us to compare the impact of concreteness and abstractness (due to concretism in schizophrenia) on behavioral outcome and neural activation.

#### fMRI Paradigm

The subjects are instructed to tap the fingers of their left hand on the buttons of a response box that is fixated at the subject's left leg. Subjects are asked to tap with their left forefinger for videos with concrete content and with their left middle finger for videos with abstract content.

Imaging data are collected with a 3 T whole body MRI system (SIEMENS MAGNETOM TrioTim syngo MR B17) equipped with a standard head coil. Structural image acquisition consists of 128 T1 weighted sagittal slices (slice thickness = 1.6 mm; FoV = 260 mm; TR = 3.15 s; TE = 1.37 s). To measure BOLD changes in brain activity during acquisition, T2* weighted gradient echo planar imaging (EPI) with 34 slices covering the whole brain will be used (voxel size = 3 x 3 x 4 mm; descending slice acquisition; slice thickness = 4.0 mm; TR = 1650 ms; TE = 25 ms; flip angle = 70°; FoV = 192 mm; GRAPPA = 2). Slices are adjusted after the anterior commissure posterior commissure (AC- PC) line. In the three measurements (A, B and C), 936 functional images are acquired during acquisition phase in the passive perception task and 666 in the memory task (n-back task). A gradient echo field map sequence is measured before the functional runs to get information for unwarping B0 distortions.

Data will be analyzed using standard procedures of Statistical Parametric Mapping (SPM12 (85), RRID: SCR_007037) implemented in MATLAB R2018b (MATLAB (86), RRID: SCR_001622). Unwarping and realignment, slice time correction, coregistration, segmentation and normalization to the standard space of the Montreal Neurological Institute brain (MNI-brain) as well as smoothing will be performed.

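### In the familiarization-session decision task, finger and content are aliased on correct trials, so the claimed concrete-abstract main effect cannot be separated from a finger effect

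*Protocol article*

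**What the plan says.** All places are in the Familiarization Session part of the protocol article's Methods, unless another heading is named.

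- **fMRI Tasks.** Before and after the short training, "participants are asked to decide whether the sentences presented to them were concrete or abstract (decision task"). The stated use is to "compare the impact of concreteness and abstractness (due to concretism in schizophrenia) on behavioral outcome and neural activation".
- **fMRI Paradigm.** All answers are given with the left hand: "The subjects are instructed to tap the fingers of their left hand on the buttons of a response box". One mapping is described, without exception: subjects are to "tap with their left forefinger for videos with concrete content and with their left middle finger for videos with abstract content".
- **Stimuli.** "Altogether, we use two categories of videos in the familiarization session": concrete and abstract sentences, both without gesture. The only balancing described is "We developed four different counterbalanced versions of stimuli presentation to avoid sequence effects".

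In the main program (The MSG Training Program, fMRI Paradigm), the passive task at A, B and C uses the forefinger for every video. The decision task appears neither under Aims and Objectives nor under Outcome Measures and End Points.

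**The concern.** A contrast between two stimulus categories is interpretable only if nothing else changes with the category. Here the responding finger changes with it, in the same direction for every subject. If the middle finger of the left hand is slower, less accurate or differently represented in motor cortex than the forefinger, the abstract condition inherits that difference. It could then look like a concreteness effect, or hide one.

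Concretism is one of the deficits the training addresses, and this is the only scanner task in which subjects classify content as concrete or abstract. The comparison is therefore likely to be reported if the text stands. Because the link is built into data collection, no later analysis can undo it for the main effect without an assumption about the finger effect.

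**Working it through.** The plan gives no figure to reproduce, so the check is whether the two effects can be separated.

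**1. Aliasing.** Code content as +1 (concrete) or −1 (abstract) and finger as +1 (forefinger) or −1 (middle finger). Under the fixed mapping, finger = content × correctness.

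- Correct trials: finger = content. The design with intercept, content and finger has rank 2 with 3 columns, so the correlation is 1 and the variance inflation factor is infinite.
- All trials, at accuracy a (assumed, since the article gives none), with balanced categories: r = 2a − 1 and VIF = 1/(1 − r²).

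| Assumed accuracy | r | VIF |
|---|---|---|
| 95% | 0.90 | 5.3 |
| 90% | 0.80 | 2.8 |
| 80% | 0.60 | 1.6 |

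This separation comes only from errors. With intercept, content, correctness, content × correctness and finger, the rank is 4 of 5 columns, because finger is the content × correctness term. Using error trials to isolate the finger effect therefore assumes that errors act alike in both content types.

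**2. Which contrasts carry the finger effect.** Let β be the true abstract-minus-concrete difference and φ the middle-minus-forefinger difference.

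- Main effect: β + φ. Exposed.
- Concreteness × time: (β_post + φ) − (β_pre + φ) = β_post − β_pre. Unaffected if φ is constant over time.
- Concreteness × group: (β_P − β_C) + (φ_P − φ_C). Unaffected if φ is equal in patients and controls; exposed only if it differs.
- Contrasts within concrete or within abstract items, such as trained versus untrained sentences: one assigned finger, so φ drops out.

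**3. Illustrative size, reaction time only.** All inputs except n = 30 per subject group (Setting) are assumptions: β = 0; φ = 10, 20 or 30 ms; SD of the within-person difference 60 to 100 ms; two-sided 5% one-sample t-test (critical value 2.045 on 29 df). Noncentrality = (φ/SD) × √30.

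| φ | SD 100 ms: noncentrality, rejection | SD 60 ms: noncentrality, rejection |
|---|---|---|
| 10 ms | 0.55, 8% | 0.91, 14% |
| 20 ms | 1.10, 19% | 1.83, 42% |
| 30 ms | 1.64, 36% | 2.74, 75% |

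**4. What a reversed mapping gives.** Under the present mapping the contrast is β + φ; under the reversed mapping it is β − φ. Their equally weighted mean is β. If 18 patients have the present mapping and 12 the reversed one, a simple mean over 30 would leave φ × (18 − 12)/30 = 0.2φ, so equal weights are needed. The variance factor is (1/18 + 1/12)/4 = 0.0347, against 1/30 = 0.0333, a ratio of 1.04.

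**The case against.** The strongest reply is that this does not touch what the trial sets out to show. The session exists to accustom subjects to the scanner and the procedures and so to limit dropout. Neither the objectives nor the listed outcomes use the decision task. The scanner contrast of concrete and abstract content that the outcomes do use comes from passive viewing at A, B and C, where every video gets the same finger. Behavior by speech content is also followed in the training tasks over eight sessions, so concretism is not assessed here alone. All of this stands, and it limits the reach of the point.

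A reader might go further and infer that the trial's concrete-abstract results, or its patient-control comparison, are confounded as a whole. The documents do not support that. The interactions cancel a finger effect that is constant over time or equal in both groups. A larger finger effect in patients is possible: the left hand is the non-dominant one for the patients described so far, and limb apraxia is tested in patients. But nothing in the article shows a difference between the groups.

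Two further replies stand in part. The article expects neural change in left temporal and left inferior frontal regions, and a finger difference in the left hand has no obvious route to a spurious effect there; the neural exposure is clearest in motor and sensorimotor areas. The reaction-time rates rest on assumed inputs and span 8% to 75%, so they illustrate the mechanism and do not estimate its size.

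What the reply does not rescue is the comparison that the fMRI Tasks section claims for this task.

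**Conclusion.** The point holds for the concrete-abstract main effect in the familiarization-session decision task. With one mapping for all subjects and only two video categories, that effect is not identifiable on correct trials, and varying the stimulus presentation does not help. The patient-control comparison of this contrast is exposed only if the finger effect differs between the groups. The concreteness × time contrast and contrasts within one content type are sound, the former provided the finger effect is constant over time. Listed objectives and outcomes are unaffected.

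The aliasing follows from the text and needs no assumption beyond the mapping having been applied as written. The size of the bias cannot be derived from the documents. The point is worth acting on because the remedy is cheap and decides whether the stated comparison can be made, but it should not be presented as a threat to the trial's main results.

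**What to change.** 1. **Participants who have not yet had this session.** Assign the reversed mapping to part of them, so that its overall share is similar in patients and controls. Tie the mapping to the existing stimulus versions and enter it as a factor, with equal weights for the two mappings in every concrete-abstract contrast of this task. The number still to be run is not stated. Under Trial Status, 18 patients and three controls had completed training by the end of March 2019, but the session precedes training, so others may already have done it.
2. **Data on one mapping only.** Report concreteness × time, or contrasts within one content type, and do not interpret the concreteness main effect. Amend the claim in the fMRI Tasks section to match.
3. **If the mapping was in fact swapped across subjects,** correct the fMRI Paradigm section and state how it was assigned.

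The cost is a changed instruction and changed response coding, with no added scans or participants. With an 18/12 split the variance rises by about 4%; fewer remaining patients would make the split less even and raise it further. Among patients, a late switch also partly confounds mapping with enrolment period: if the finger effect differs between early and late patients (φ₁ and φ₂), the equally weighted mean keeps a bias of (φ₁ − φ₂)/2. State this as a limitation. Controls are less affected, since only three had completed training.

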#### Short Speech-Gesture Training

Between the two fMRI measurements in the familiarization session, participants are trained with videos containing sentences with and without gesture. They are asked to attentively watch the videos. Some of the videos presented in bimodal condition (speech accompanied by gesture) are to be imitated by the participants.

#### Memory Task After Post-fMRI

After post-fMRI measurement, participants conduct a memory task, where audios from the sentences are presented, that also appeared in the fMRI measurement's and short speech-gesture training's videos. Participants are asked to decide whether they know the presented sentences from the short speech-gesture training and if yes, if the videos appeared with or without gesture and if the participants were asked to imitate the videos during the short training. That is, participants have four options to answer:Sentence was not trained (unimodal control condition: S_C)Sentence appeared in the training without gesture (unimodal perception: S_P)Sentence appeared in the training with gesture (bimodal perception: SG_P)Sentence with gesture was asked to be imitated in the training (bimodal imitation: SG_I)

### The MSG Training Program

#### Social and Quality of Life Questionnaires

To assess the effect of the gesture training on social functioning and quality of life, participants (patients and controls) are asked to complete psychological questionnaires about social life [SASS – Soziale Aktivität Selbstbeurteilungs-Skala (87): satisfying validity and reliability with cronbach alpha = 0.89 (88)] and quality of life [SWLS – Satisfaction with Life Scale (89): satisfying validity and reliability with cronbach alpha = 0.87 (81)] before and after the training program (assessment A/B and B/C, respectively). Furthermore, patients are asked about schizophrenia symptoms to assess positive and negative symptoms [(through SAPS (78)/SANS (79) and PSP-Scale (80)] as well as gesture performance [through the short version of TULIA—Test of Upper Limb Apraxia(82) and BAG—brief self-rating scale for the assessment of individual differences in gesture perception and production (83)] before they start with the training. The ratings in the questionnaires will later be correlated with the behavioral and neural outcome of the training to evaluate the effects on social life and quality of life.

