## Methods

### Aims and Objectives

This study aims to investigate the behavioral and neural effects of a new speech-gesture-training program for patients with schizophrenia.

The objectives are to:Assess the acceptability of a MSG training in patients.Assess the training effects in terms of n-back task performance for speech and gesture videos in dependency of speech content.Assess the training effects on the neural correlates of speech-gesture integration and working memory in dependency of speech content.Assess the behavioral outcomes of MSG training tasks in association to neural activation for each condition of stimuli (see stimuli section for more information).Assess the effect of gesture training on scores of psychological questionnaires relating to social performance and quality of life.

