#### Inclusion of Participants

In a telephone screening, interested persons are called by one of the researchers to make sure that both their status of physical health and capability to participate in an fMRI study meet our conditions. Inclusion and exclusion criteria are part of this screening as well as a questionnaire about the progress, the individual core symptoms of schizophrenia and medication in patients.

Subjects *are eligible* for study entry if they meet the following criteria:Aged between 18 and 60 years.Capacity to give informed consent.

Additional criteria, patients only:Diagnosis of schizophrenia after DCM-5 criteria.Relatively stable symptoms (no acute psychosis).

To evaluate the stadium and type of symptoms of the patients as well as for safety reasons, we additionally conduct a pre-scan interview with the patients including questions concerning the illness and medication as well as three standardized psychological questionnaires for schizophrenia [SAPS (78)/SANS (79) and PSP-Scale (80)].

Subjects *are not eligible* if any of the following criteria are present:No capacity to give informed consent.Risk of suicide necessitating hospitalization.Physical illnesses that interfere with the planned measurements.Medical contraindication against fMRI measurements.Pregnancy.Contraception per intrauterine contraceptive device.

Additional criterion for exclusion, control subjects only:Diagnosis of psychological diseases, especially schizophrenia.

If interested subjects meet the criteria, they meet with a member of the research team to go through the study information. Inclusion and exclusion criteria are confirmed along with the assessment of positive and negative symptoms of schizophrenia as well as gesture performance (for patients), social activity and quality of life (all participants). Participants are informed that they are free to withdraw at any time without giving reasons and without prejudicing any further treatment.

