### Outcome Measures and End Points

Our interest is the behavioral outcome of an MSG training on communication, social skills and quality of life as well as its neural correlates in brain regions.

Proposed behavioral outcomes are:

Behavioral data:Behavioral outcomes (n-back task performance: accuracy and reaction time for each condition) in interaction with treatment group (wait-training group vs. training-follow-up group) and time point (assessment A vs. B and B vs. C)Behavioral outcomes (n-back task performance: accuracy and reaction time for each condition) in interaction with subject group (patients vs. control group) and time point (assessment A vs. C)Behavioral improvement during training (speech-gesture matching and working memory performance: reaction time and percent correct, SG fluency performance: number of correct items and gesture imitation: experimenter evaluation of accuracy) as interaction with group (patients vs. control group) and time point (training session one to eight)Neural data:Neural activation (whole brain and specific regions of interest [ROI]: the left inferior frontal gyrus [IFG]) during the passive viewing and the n-back task in interaction with video condition, treatment group (wait-training group vs. training-follow-up group) and time point (Assessment A vs. B and B vs. C)Neural activation (whole brain and specific ROIs: STS and left IFG) during the passive viewing and the n-back task in interaction with video condition, subject group (patients vs. control group) and time point (Assessment A vs. C)Social data (self-report):Social functioning as measured by SASS – Soziale Aktivität Selbstbeurteilungs-Skala(87) in interaction with time point (*t_3_* vs. *t_5_*) and group (patients vs. control group)Quality of life as measured by SWLS – Satisfaction with Life Scale(89) in interaction with time point (*t_3_* vs. *t_5_*) and group (patients vs. control group)Communication skills as measured by a questionnaire for relatives of the patients (created for this study by our research team) in correlation with neural and behavioral measures of MSG related improvements (e.g., *t_3_* vs. *t_5_*)

In addition to that, we are planning to correlate the neural and behavioral outcomes as well as neural and social and behavioral and social outcomes.

For a summary/overview of the study see **Figure 2**.

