The present study offers an intensive MSG training to patients with schizophrenia and a healthy control group and correlates the behavioral outcomes from this training with neural activation before and after the training as well as with social skills and quality of life. The randomized controlled trial with waiting list and follow-up measurement enables us to demonstrate not only the effect of the gesture training on behavior, self-reports and neural correlates but also to explore long-term effects and potential predictors of treatment outcome (44, 98). While it remains to be seen whether changes can be detected within our proposed measures, the intervention seems at least to be profitable to the patients, who have completed the measurements and trainings so far (see section 2.6 *Trial Status*).

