### Advantages

Highlighting the advantages of our novel MSG training intervention, in contrast to regular interventions, coupling of social-communicative skills along with motoric features are directly trained in our program. Beyond that, extra-linguistic and pragmatic information found in meaningful hand and arm movement interpretation is addressed. The playful character of the exercises simultaneously trains neurophysiological capacities and may result in a generalisation of possible training effects. Concerning the data that we collect, one of the current study's strengths is the brain imaging techniques that allow us to investigate the neural plasticity effects of the MSG training on social-cognitive abilities in patients with schizophrenia. Furthermore, we focus on cognitive aspects of gesture to facilitate social-cognitive functioning in everyday life. Due to the possible impact dysfunctional communication has on life quality, transfer in everyday life social functioning is one of our main objectives.

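### The SASS and SWLS outcomes are defined as time by patients versus controls, both of whom are trained, so the listed contrast does not estimate the training effect on social functioning and quality of life

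*Protocol article*

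**What the plan says.** Aims and Objectives lists as one aim: "Assess the effect of gesture training on scores of psychological questionnaires relating to social performance and quality of life". The Discussion (Current Study) says that the randomised waiting-list design "enables us to demonstrate not only the effect of the gesture training on behavior, self-reports and neural correlates", and Advantages adds that "transfer in everyday life social functioning is one of our main objectives".

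The Setting section names questionnaires among the outcomes used to compare both the two subject groups and the two intervention groups.

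Outcome Measures and End Points is more specific. SASS and SWLS are each to be examined "in interaction with time point (*t_3_* vs. *t_5_*) and group (patients vs. control group"). In the same list, n-back performance is examined "in interaction with treatment group (wait-training group vs. training-follow-up group) and time point (assessment A vs. B and B vs. C"), and neural activation has a matching treatment-group line.

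The section on the social and quality-of-life questionnaires schedules the two scales "before and after the training program (assessment A/B and B/C, respectively"). Read with Intervention Groups and Randomization, this means A and B in the training-follow-up arm and B and C in the wait-training arm. That section also states that healthy subjects take part in the training. Inclusion of Participants mentions an assessment at entry of "social activity and quality of life (all participants"), without naming the instrument.

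**The concern.** The waiting arm is in the design to separate the effect of training from usual treatment, repetition and the passage of time; the legend to Figure 1 says so. For the two self-report scales, the outcome list does not use it. Patients versus controls is not trained versus untrained, because both groups receive the programme. The listed interaction asks whether patients change more than healthy people do when both are trained, which is not the question in the aims.

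Two errors could follow. A real benefit shared by both groups would not show in the interaction. A change in patients alone, unrelated to training, could be read as a training effect. These are self-reports from people who know whether they have been trained, and transfer to everyday life is called a main objective, so the choice of comparator matters for the conclusions.

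**Working it through.** **1. What the listed contrast estimates.** Let τ be the change from time or repeat answering and δ the training effect, with subscripts P (patients) and C (controls).

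- Pre-post change in patients: τ_P + δ_P
- Pre-post change in controls: τ_C + δ_C
- Listed interaction: (τ_P − τ_C) + (δ_P − δ_C)

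Examples in SD units:

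- τ = 0 and δ = 0.5 in both groups: the interaction is 0 despite a real effect.
- τ = 0.3 in both, δ = 0: the interaction is 0, so shared drift does cancel.
- τ_P = 0.3, τ_C = 0, δ = 0: the interaction is 0.3 with no training effect.

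**2. How often patient-only drift would be declared significant.** Inputs: 30 per subject group (Setting). Assumed: two-sided 5% level, SD 1, pre-post correlation 0.6, no training effect.

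- SD of a change score: √(2 × (1 − 0.6)) = 0.894
- SE of the interaction: 0.894 × √(1/30 + 1/30) = 0.231

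| Drift in patients beyond controls (SD) | Drift / SE | Rejection rate |
|---|---|---|
| 0 | 0 | 5% |
| 0.10 | 0.43 | about 7% |
| 0.15 | 0.65 | about 10% |
| 0.30 | 1.30 | about 25% |

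Varying the assumptions over correlations of 0.5 to 0.8 and patient-only drifts of 0.2 to 0.4 SD gives rates from 12% to 67%. The article gives no figure for drift or correlation.

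**3. Whether a waiting comparison exists in the planned data.** At assessment B the training-follow-up arm has been trained, the wait-training arm has only waited, and both complete the scales. Time cancels between randomised arms, so the contrast at B in patients estimates δ_P, plus any difference in expectation. Repeat answering also cancels, provided both arms have completed the forms equally often before B. On the printed schedule they have not: the training-follow-up arm has a form at A and the wait-training arm does not.

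**4. How precise that comparison is.** The legend to Figure 1 gives 20 waiting and 10 trained patients. Assumed: two-sided 5% level, SD 1.

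- SE: √(1/20 + 1/10) = 0.387
- 95% CI half-width: 1.96 × 0.387 = 0.76 SD
- Detectable difference at 80% power: (1.960 + 0.842) × 0.387 = 1.09 SD, or about 1.12 SD with the t distribution
- Power (t distribution): 24% at 0.5 SD and 51% at 0.8 SD
- With a baseline score correlated r with the outcome, multiply by √(1 − r²): 0.94 SD at r = 0.5 and 0.77 SD at r = 0.7

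The article gives no sample-size calculation for these scales, so there is no published figure to reproduce.

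**The case against.** **The article does name an arm comparison.** The Setting section lists questionnaires among outcomes compared between the intervention groups. A reader might infer from the outcome list that the trial discards randomisation for self-reports altogether, but the article does not support that. What stands is a conflict: a general statement promises the comparison, and the specific list defines these two outcomes without it.

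**Controls do some work.** It is tempting to say that nothing separates training from time. That is too strong, because drift shared by patients and controls cancels in the interaction. Likewise, an uncontrolled pre-post test in patients would reject far more often (about 43% at 0.3 SD drift and correlation 0.6), but that test is not listed for SASS or SWLS and the figure should not be held against the plan.

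**The schedule is not fully known.** The labels t3 and t5 are not defined in the text, and Figure 2 was not available for this review. A reader might infer that the training-follow-up arm has no questionnaire at C, so that lasting benefit cannot be seen. That follows only if the A/B and B/C wording is the complete schedule. If t3 and t5 meant A and C, the main point would remain: there would still be no treatment-group term, and both arms would be trained by C.

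**The arm comparison has its own limits.** Participants at B know whether they have been trained, so expectation stays mixed with training. With 20 versus 10 patients the result may well be inconclusive. Both objections stand. They limit what can be claimed from the comparison, but they do not make patients versus controls an estimate of the training effect.

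**Conclusion.** The point holds in a limited form. The SASS and SWLS contrast in Outcome Measures and End Points does not estimate the training effect set as an objective, and it does not match the Setting section or the claim about self-reports in the Discussion. This follows from the design, since both subject groups are trained, and does not depend on the simulated sizes. Those sizes rest on assumed drift and correlation: the false-positive rate is nominal if drift is equal and rises to about 10% or 25% with patient-only drifts of 0.15 or 0.3 SD.

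A randomised comparison at B is available from data already scheduled. It deals with time and regression to the mean, and with repeat answering if the forms are given equally often in both arms. It does not deal with expectation, and in patients it can detect only about 1.1 SD at 80% power without baseline adjustment.

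**What to change.** - **Add the contrast.** In Outcome Measures and End Points, for SASS and SWLS in patients, compare the arms at assessment B (training-follow-up trained, wait-training not yet trained). Adjust for the inclusion score if that assessment used SASS and SWLS. Report an estimate with a 95% confidence interval. Keep patients versus controls as a secondary, descriptive contrast.
- **Complete the schedule for participants not yet measured.** If the current schedule lacks them, give both forms at A in the wait-training arm and at C in the training-follow-up arm.
- **Reconcile the text.** Align the Setting section, the questionnaire schedule, the outcome list and the Discussion, and state in the text which assessments t3 and t5 are.
- **Soften the claim.** Say in the Discussion that the self-report comparison is unblinded, imprecise and open to expectation.

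**Cost.** The contrast needs only analysis wording. The added forms are two short self-reports at visits that already exist. They cannot be obtained for the 18 patients (of 30 planned) whom Trial Status reports as having finished training, so for those patients the comparison at B rests on what was collected. The price in precision is the wide interval shown above.
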